### 2.5. Participants and Recruitment

Both males and females of diverse races and ethnicities, who live in Hertfordshire and its surrounding areas, will be recruited. Recruiting materials will be placed via local Crohn’s and Colitis UK (CCUK) network, the CCUK website as well as using social media. We envisage that participant recruitment will commence in September of 2023.

## 3. Procedures

### 3.1. Intervention and Control Groups

After completing their initial data collection, participants will be given Montmorency tart cherry concentrate or a placebo.

#### 3.1.1. Montmorency Tart Cherry

For a period of six weeks, participants assigned to this group will consume 60 mL of Montmorency tart cherry concentrate (Montmorency Tart Cherry Juice Concentrate, King Orchards, Kewadin, MI, USA) each day [36,37,38]. The concentrate will then be diluted with 100 mL of water to make each 30 mL serving into a 130 mL beverage. Each day, 130 mL of the tart cherry supplement will be taken in two equal doses: in the morning and in the evening. A 30 mL dose of Montmorency tart cherry concentrate includes 80 Kcal, 19 g of carbohydrates, of which 15 g are sugars, 1.1 g of protein, and 1 g of fibre, according to the manufacturer. Previous phytochemical analyses have shown that 30 mL of Montmorency tart cherry concentrate contains 9.117 mg/mL of anthocyanins and 6.63 total phenolics/mL (expressed as gallic acid equivalents) [38,39]. However, to quantitatively assess the anthocyanin and phenolic contents of the supplement batch that is utilized in this trial, a phytochemical content analysis of the Montmorency tart cherry concentrate batch will be completed by the manufacturer. Anthocyanin and phenolic contents will be examined using the pH-differential and modified Folin–Ciocalteu colorimetric methods, respectively [40].

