#### 3.1.2. Placebo

The placebo will be prepared in accordance with previous trials, that have demonstrated this form of placebo production to be an efficient blinding strategy [36,37]. For a total of six weeks, participants assigned to the placebo group will ingest 60 mL each day [36,37]. The placebo will also be diluted with 100 mL of water and taken twice day in equal amounts, just like the supplement condition. Using a magnetic stirrer (Stuart Scientific, Staffordshire, UK) and stir bar (Fisher Scientific, Waltham, MA, USA), the placebo will be prepared by combining 100% unflavored maltodextrin carbohydrates (MyProtein, Cheshire, UK) with drinking water. Maltodextrin will be combined with water to make 1.0 litre of placebo concentrate, resulting in 20 g of maltodextrin per 30 mL dosing, resembling the carbohydrate/sugar content of the Montmorency tart cherry supplement. In order to replicate the colour of the Montmorency tart cherry concentrate, equal amounts of red and black food colouring will be added. To achieve the desired flavour, cherry flavdrops (1 mL) (MyProtein, Cheshire, UK) will then be added. A 30 mL dose of placebo concentrate includes 0 mg of anthocyanins and contains 100 Kcal, 20 g of carbohydrates, of which 0 g are sugars, as well as 0 g protein and 0 g fibre.

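### The daily volume of tart cherry drink, as worded, carries half the daily concentrate stated in the same paragraph, and the two figures need reconciling

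*Protocol article*

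**What the plan says.** Section 3.1.1 makes three statements about volume in the active arm:

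- Daily concentrate, over six weeks: "participants assigned to this group will consume 60 mL of Montmorency tart cherry concentrate" each day.
- Dilution: the concentrate is "diluted with 100 mL of water to make each 30 mL serving into a 130 mL beverage".
- Daily intake of the drink: "Each day, 130 mL of the tart cherry supplement will be taken in two equal doses: in the morning and in the evening".

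The same section gives nutrient content for a 30 mL dose: "A 30 mL dose of Montmorency tart cherry concentrate includes 80 Kcal, 19 g of carbohydrates, of which 15 g are sugars". It also gives a published anthocyanin concentration: "30 mL of Montmorency tart cherry concentrate contains 9.117 mg/mL of anthocyanins". The batch used in the trial is to be assayed separately.

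For the control arm, section 3.1.2 says "participants assigned to the placebo group will ingest 60 mL each day" and then: "The placebo will also be diluted with 100 mL of water and taken twice day in equal amounts, just like the supplement condition". It gives no total for the diluted drink.

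Sections 1.2 and 4 describe supplementation as twice daily, without a volume. Section 3.4 plans between-arm comparisons of compliance and of experimental anthocyanin, energy and sugar intake.

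**The concern.** The dilution rule fixes how much concentrate a given volume of drink contains. A daily volume of concentrate and a daily volume of drink must therefore agree, and in section 3.1.1 they do not. The drink sentence gives 130 mL as the day's amount and divides it into two equal parts. Under the stated dilution, 130 mL of drink is a single serving.

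This is the definition of the trial's only experimental intervention. Someone preparing participant instructions, checking returned product or replicating the trial from this text could take either sentence and arrive at exposures that differ by a factor of two. The compliance and experimental intake summaries in section 3.4 also need one prescribed daily amount to refer to, and the article gives two.

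**Working it through.** **Inputs (sections 3.1.1 and 3.1.2)**

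- Concentrate per serving: 30 mL. Water per serving: 100 mL.
- Stated daily concentrate: 60 mL.
- Stated daily drink: 130 mL in two equal doses.
- Content per 30 mL: 80 kcal, 15 g sugars. Anthocyanins: 9.117 mg/mL (earlier analyses, not the trial batch).

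**Step 1. The dilution figure is consistent.** 30 + 100 = 130 mL. The fraction of concentrate in the drink is 30/130.

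**Step 2. Drink needed to deliver the stated 60 mL per day.** Servings = 60/30 = 2. Drink = 2 × 130 = 260 mL per day.

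**Step 3. Concentrate in the stated 130 mL per day.** 130 × 30/130 = 30 mL per day. In two equal doses, each is 130/2 = 65 mL and carries 65 × 30/130 = 15 mL of concentrate.

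**Step 4. Can the 60 mL figure be recovered?**

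| Reading | Drink per day | Concentrate per day | Agrees with 60 mL? |
|---|---|---|---|
| 130 mL is the daily total (as worded) | 130 mL | 30 mL | No |
| 130 mL on each of two occasions | 260 mL | 60 mL | Yes |
| All 60 mL mixed once with 100 mL of water (160 mL), 130 mL of it drunk | 130 mL | 130 × 60/160 = 48.75 mL | No, and it breaks the stated dilution |

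Only the per-occasion reading reproduces 60 mL, and it is not what the sentence says.

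**Step 5. Size, from the article's own contents.**

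| | 60 mL/day | 30 mL/day |
|---|---|---|
| Energy | 2 × 80 = 160 kcal | 80 kcal |
| Sugars | 2 × 15 = 30 g | 15 g |
| Anthocyanins (illustrative) | 60 × 9.117 = 547 mg | 30 × 9.117 = 274 mg |
| Concentrate over 42 days | 60 × 42 = 2,520 mL | 30 × 42 = 1,260 mL |

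**Step 6. Placebo.** Section 3.1.2 states 60 mL per day, 100 mL of water and two equal drinks. If the water is per drink, the day's total is 2 × (30 + 100) = 260 mL. If it is per day, the total is 60 + 100 = 160 mL. Both carry the stated 60 mL, so the placebo section does not contradict itself. What it leaves open is the diluted volume, for which it points back to section 3.1.1.

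**The case against.** The best reply is that one sentence is out of line and everything else agrees. The 60 mL daily figure, the 30 mL serving, the nutrient content quoted per 30 mL dose, the 60 mL placebo figure and the twice-daily schedule all fit together. The article never describes a 65 mL drink or a 15 mL portion of concentrate; those numbers appear only when the sentence is taken at its word. If 130 mL means the volume of each drink, the conflict disappears. That is a fair account of how the wording may have arisen, and it stands as a plausible explanation. It does not remove the inconsistency, because the reader has to override an explicit dosing sentence to reach it.

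A reader might go further and infer that the arms could receive different regimens, so that the between-arm contrast or the blinding is at risk through unequal drink volumes. The article does not support that. Section 3.1.2 ties the placebo regimen to the supplement regimen and gives the same 60 mL per day, so matching is required under either reading. The participant instructions are not shown, and nothing indicates that they carry the discrepancy or that the arms are instructed differently.

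Two further points stand in part. Section 3.4 does not say how compliance or the experimental intakes are calculated, and an article may leave that to a fuller document. The request is therefore only that those calculations use the reconciled figure. The milligram values are also not trial values, since the batch is to be assayed. The factor of two does not depend on them.

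**Conclusion.** The point holds as an internal contradiction in section 3.1.1. As worded, the daily drink carries 30 mL of concentrate against a stated 60 mL, a two-fold difference, and no other section explicitly settles it. This rests only on the stated dilution and on reading the drink sentence literally. It may well be a drafting slip. The article does not show that participants will receive, or have received, half the intended amount, and no view is taken on which volume is intended. The placebo section inherits an uncertainty about the water volume but not the contradiction. Randomisation, the primary outcome, the sample size and the analysis model are unaffected. The correction is still needed, because the figure defines the intervention.

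**What to change.** The investigators should reconcile sections 3.1.1 and 3.1.2 so that three quantities are stated once and identically for both arms: concentrate per day, diluted volume per drink, and number of drinks per day. The text should also say whether the 100 mL of water is added per drink or per day. The participant instructions should then be checked against that statement. The reconciled daily amount should be the reference for compliance and for the experimental anthocyanin, energy and sugar intakes in section 3.4, with the assayed batch value replacing the published anthocyanin concentration. Which volume is intended is for the investigators to state.

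The cost is a wording correction in two paragraphs and a check of the instructions. No change to the design, sample size or analysis follows from it.

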#### 3.1.2. Placebo

The placebo will be prepared in accordance with previous trials, that have demonstrated this form of placebo production to be an efficient blinding strategy [36,37]. For a total of six weeks, participants assigned to the placebo group will ingest 60 mL each day [36,37]. The placebo will also be diluted with 100 mL of water and taken twice day in equal amounts, just like the supplement condition. Using a magnetic stirrer (Stuart Scientific, Staffordshire, UK) and stir bar (Fisher Scientific, Waltham, MA, USA), the placebo will be prepared by combining 100% unflavored maltodextrin carbohydrates (MyProtein, Cheshire, UK) with drinking water. Maltodextrin will be combined with water to make 1.0 litre of placebo concentrate, resulting in 20 g of maltodextrin per 30 mL dosing, resembling the carbohydrate/sugar content of the Montmorency tart cherry supplement. In order to replicate the colour of the Montmorency tart cherry concentrate, equal amounts of red and black food colouring will be added. To achieve the desired flavour, cherry flavdrops (1 mL) (MyProtein, Cheshire, UK) will then be added. A 30 mL dose of placebo concentrate includes 0 mg of anthocyanins and contains 100 Kcal, 20 g of carbohydrates, of which 0 g are sugars, as well as 0 g protein and 0 g fibre.

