### 3.4. Statistical Analysis

Continuous experimental variables will be presented as mean values along with their corresponding standard deviations. To compare participant characteristics at baseline, as well as compliance levels, experimental anthocyanin intake, experimental energy intake, and experimental sugars (g/day) between the trial arms, between-group linear mixed effects models will be utilized. In these models, the group will be treated as a fixed factor, and random intercepts will be included for participants.

All analyses of the intervention-based data will follow an intention-to-treat approach. To determine the effects of the intervention on all of the outcome measures, differences in the changes from baseline to 6 weeks between the two trial arms will be examined using linear mixed-effects models with a group modelled as a fixed factor and random intercepts by participants adopted. For linear mixed models, the mean difference between groups in changes from baseline to 6 weeks (*b*) and 95% confidence intervals of the difference will be presented. Effect sizes were calculated for the changes from baseline to 6 weeks between the two groups, using Cohen’s *d*, in accordance with McGough & Faraone [51]. Cohen’s d values will be interpreted as 0.2 = small, 0.5 = medium, and 0.8 = large [52]. The efficacy of blinding will be assessed using a one-way chi-square (*Χ*^2^) goodness-of-fit test. Chi-square analyses will be calculated using Monte-Carlo simulation to determine probability values. All statistical analyses will be performed using SPSS v28 (IBM Inc., SPSS, Chicago, IL, USA), and statistical significance will be considered at a *p* ≤ 0.05 level.

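### The placebo's stated energy and carbohydrate cannot both be right: 20 g of carbohydrate with no protein or fibre gives about 80 kcal per 30 mL dose, not 100 kcal

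*Protocol article*

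**What the plan says.** All references are to the protocol article.

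- **Placebo composition (section 3.1.2).** A 30 mL dose of concentrate "contains 100 Kcal, 20 g of carbohydrates, of which 0 g are sugars, as well as 0 g protein and 0 g fibre". The preparation instruction in the same section sets the quantity separately, "resulting in 20 g of maltodextrin per 30 mL dosing", and gives the aim as "resembling the carbohydrate/sugar content of the Montmorency tart cherry supplement". The ingredients named are maltodextrin, drinking water, food colouring and 1 mL of cherry flavouring.
- **Cherry composition (section 3.1.1).** A 30 mL dose "includes 80 Kcal, 19 g of carbohydrates, of which 15 g are sugars, 1.1 g of protein, and 1 g of fibre".
- **Daily amount.** Both arms take 60 mL of concentrate a day, that is, two 30 mL doses: "participants assigned to this group will consume 60 mL of Montmorency tart cherry concentrate" (section 3.1.1) and "participants assigned to the placebo group will ingest 60 mL each day" (section 3.1.2).
- **Use in the analysis (section 3.4).** Between-group models are planned for compliance and for "experimental anthocyanin intake, experimental energy intake, and experimental sugars (g/day) between the trial arms". The section does not say where the per-dose values for these intakes will come from.

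**The concern.** The two drinks carry almost the same carbohydrate (20 g placebo, 19 g cherry), and the cherry dose also contains protein and fibre. Yet the placebo is credited with 20 kcal more per dose. Nothing listed in the placebo accounts for that excess.

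The consequence depends on which figure is wrong.

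- **The energy figure is wrong.** If the printed values feed the planned comparison of energy intake, a difference between arms is built in before anyone has drunk anything. Intake would then be a fixed number multiplied by compliance, so the model could report as a finding what is only a labelling error.
- **The gram figure is wrong.** The drinks would then differ physically in both carbohydrate and energy, and the carbohydrate resemblance claimed in section 3.1.2 would fail.

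Either way, a reader cannot tell from the text whether the placebo and the active drink supply the same energy.

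**Working it through.** **Inputs, per 30 mL dose**

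| | Energy (stated) | Carbohydrate | Protein | Fibre | Source |
|---|---|---|---|---|---|
| Placebo | 100 kcal | 20 g | 0 g | 0 g | section 3.1.2 |
| Cherry | 80 kcal | 19 g | 1.1 g | 1 g | section 3.1.1 |

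The document gives no energy conversion factor. I assume 4 kcal/g for carbohydrate and for protein, with 3.75 to 4.2 kcal/g as the range for carbohydrate.

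**Step 1: does the method reproduce the cherry figure?** (19 + 1.1) × 4 = 80.4 kcal, against 80 stated. Treating fibre differently changes little. Taking the fibre out of the carbohydrate and counting it at 2 kcal/g gives 18 × 4 + 1.1 × 4 + 2 = 78.4 kcal. Adding it on top gives 19 × 4 + 1.1 × 4 + 2 = 82.4 kcal. The method works for the active arm.

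**Step 2: does it reproduce the placebo figure?** 20 × 4 = 80 kcal, against 100 stated. Over the range, 20 × 3.75 = 75 kcal and 20 × 4.2 = 84 kcal. The stated pair implies 100/20 = 5.0 kcal/g. The excess is 20/80 = 25% of the expected value.

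**Step 3: can anything else close the gap?**

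- Rounding: in the most favourable case, 95 kcal printed as 100 and 20.5 g printed as 20, the ratio is still 95/20.5 = 4.63 kcal/g.
- Flavouring: allowing an extreme 9 kcal in every dose on top of the highest factor gives 84 + 9 = 93 kcal.
- Unlisted fat: the missing 20 kcal would need 20/9 = 2.2 g of fat per dose (at an assumed 9 kcal/g), and the recipe names no fat source.

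**Step 4: daily size of the discrepancy (two doses a day)**

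| | Placebo | Cherry | Difference |
|---|---|---|---|
| Stated energy, full compliance | 2 × 100 = 200 kcal | 2 × 80 = 160 kcal | 40 kcal |
| Stated energy, 80% compliance in both arms | 160 kcal | 128 kcal | 32 kcal |
| Listed nutrients at 4 kcal/g, full compliance | 2 × 80 = 160 kcal (150 to 168) | 2 × 80.4 = 160.8 kcal | −0.8 kcal |

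The 150 to 168 kcal range is for 3.75 to 4.2 kcal/g.

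**Step 5: the alternative, that 100 kcal is right.** The dose would hold 100/4 = 25 g of carbohydrate (100/4.2 = 23.8 g to 100/3.75 = 26.7 g). The daily carbohydrate would be 2 × 25 = 50 g on placebo against 2 × 19 = 38 g on cherry, with 200 v 160 kcal/day.

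**Step 6: what the batch recipe would show.** A dose of 20 g per 30 mL is 20 × 1000/30 = 667 g of maltodextrin per litre of concentrate. A dose of 25 g is 25 × 1000/30 = 833 g per litre. The two are far enough apart for the recipe record to tell which applies.

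**The case against.** The arithmetic is hard to dispute, so the case on the other side concerns its weight.

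- **This looks like a single slip.** The 20 g figure appears twice, once as a preparation target and once in the composition line, and it sits next to the cherry's 19 g, which it was meant to resemble. The 100 kcal figure appears once, with no support elsewhere. This is fair: the energy is the likelier error. But the text cannot exclude the alternative, and the recipe can, so both outcomes need a remedy.
- **The conflict rests on an outside conversion factor and on the absence of fat, which the composition line does not mention.** Both are true. However, the factor reproduces the cherry label, no value in the assumed range rescues the placebo label, and the named ingredients include no fat source. Carbohydrate is best described as the only listed energy source.
- **No energy match is claimed.** Correct. Section 3.1.2 claims resemblance in carbohydrate and sugar only, and section 3.4 plans to compare energy, not to assert equality. A 200 v 160 kcal/day result would contradict the listed nutrients but no stated design claim.
- **The effect is conditional and small.** It requires the printed values to be used in the intake comparison, which is not an efficacy outcome. Against an assumed diet of 2,000 kcal/day, 40 kcal is 2% (2.7% at 1,500 and 1.6% at 2,500). This stands, and it keeps the point minor.

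**Conclusion.** The placebo composition line is wrong as written. With 20 g of carbohydrate and no protein or fibre, the dose supplies about 80 kcal (75 to 84), not 100, or else it contains about 25 g (23.8 to 26.7) and not 20. The first is more likely, but the document does not decide between them.

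If the printed values are used, the planned comparison of supplement energy intake would show up to 40 kcal/day between arms, where the listed nutrients show essentially none. If the grams are the error, the difference is real and extends to carbohydrate, at 50 v 38 g/day.

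The conclusion rests on a carbohydrate factor of 3.75 to 4.2 kcal/g and on the named ingredients being complete. The consequence for the analysis rests further on the printed per-dose figures being its input, which section 3.4 does not state. The primary comparison, the sample size and alpha do not depend on any of this. The point is minor.

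**What to change.** Check the energy and gram figures against the maltodextrin label and the batch recipe.

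- **If the recipe uses about 667 g per litre (20 g per dose):** correct the energy in section 3.1.2 to about 80 kcal per 30 mL dose, and use that value when deriving energy intake for the comparison in section 3.4. One figure changes.
- **If it uses about 833 g per litre (25 g per dose):** correct the carbohydrate to about 25 g. Then either state that carbohydrate and energy are not matched, with the daily figures above, or prepare the placebo at 20 g per dose as intended.

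While that sentence is open, the resemblance claim would be more accurate if confined to total carbohydrate, since the disclosed sugars are 0 g v 15 g per dose.

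The cost is one label and recipe check and a small text correction, or at most a change of recipe. Recruitment and the primary analysis do not change.

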### 3.2. Data Collection

All measurements will be made inside the Physiology laboratory at the University of Hertfordshire and will be carried out in the exact same way on two occasions: at baseline and after six weeks.

#### 3.2.1. Questionnaires

The primary outcome measure for this study will be the Inflammatory Bowel Disease Quality of Life Questionnaire. Secondary questionnaires will include the simple clinical colitis activity index (SCCAI), IBD Fatigue Scale, International Physical Activity Questionnaire—Short Form (IPAQ-SF), and the Hospital Anxiety and Depression Scale. The Inflammatory Bowel Disease Quality of Life Questionnaire is a widely used and validated instrument, specifically designed for patients with IBD [41,42]. It consists of 32 items scored on a 7-point Likert scale, with higher scores indicating better IBD-related quality of life based on a range of 32–224. The questionnaire assesses four dimensions: bowel symptoms, systemic symptoms, emotional well-being, and social functioning. The simple clinical colitis activity index (SCCAI) is a validated, symptom-based index comprising six items. Scores on this index range from 0 to 19, with higher scores indicating more severe symptoms [43]. The IBD Fatigue Scale is an IBD-specific tool that evaluates fatigue in individuals with IBD [44]. It consists of two components: one estimates the level of fatigue using five questions, and the other measures the impact of fatigue on quality of life using 30 questions. Scores are calculated on a 0–4 Likert scale, with a maximum score of 120 and higher scores indicating higher levels of fatigue and greater impact on quality of life. The International Physical Activity Questionnaire—Short Form (IPAQ-SF) is a validated questionnaire consisting of nine items. It assesses physical activity across four intensity levels: vigorous-intensity activity, moderate-intensity activity, walking, and sitting. Energy expenditure is calculated in metabolic equivalents per week [45]. The Hospital Anxiety and Depression Scale is a validated 14-question scale used to assess symptoms of anxiety and depression. It comprises separate sections for depression (7 questions) and anxiety (7 questions), with scores ranging from 0 to 21 for each section. Higher scores indicate greater levels of depression or anxiety [46].

In accordance with previous trials examining the clinical efficacy of Montmorency tart cherries, participants will be required to maintain their habitual patterns throughout the intervention period and also asked to keep a 4-day diet diary prior to the baseline assessment and before the follow-up examination at the end of the 6-week treatment period [36,47,48,49]. This will ensure that there are no differences in dietary patterns between groups and that participants have not made significant changes to their nutritional approach that could influence the study outcomes. Any comorbidities and medications taken by participants will also be recorded.

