### 1.1. Rationale

There are no placebo-controlled, randomized trials examining the efficacy of Montmorency tart cherry in patients with UC. Our research [31] has revealed a strong willingness to take Montmorency tart cherry supplementation in patients with UC, demonstrating a high-level of patient engagement for a randomized clinical trial involving Montmorency tart cherry supplementation. Therefore, further exploration of the health benefits of tart cherries in patients with UC may be of both practical and clinical relevance.

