### 2.2. Inclusion Criteria

To be eligible for inclusion in this study, participants must meet the following criteria: (1) have a confirmed diagnosis of UC for a minimum of 6 months, (2) exhibit mild to moderate disease activity at the time of enrollment, (3) fall within the age range of 18 to 65 years, and (4) have maintained consistent use of medication for a minimum of 3 months. The aforementioned inclusion criteria were collectively adopted based on previous randomized trials in patients with UC [33,34]. Mild–moderate disease activity will be given a Mayo Clinic Score between 3–10, in accordance with the British Society of Gastroenterology consensus guidelines [35].

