### 2.3. Exclusion Criteria

Exclusion criteria for this trial include the presence of diabetes, HIV, rheumatoid arthritis, or any other autoimmune disease, as well as hepatitis B and C infections. Additionally, individuals with abscesses, unstable medical conditions that may hinder their ability to complete the study or known food allergies to cherries will also be excluded from participation.

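### Current users of tart cherry or other anthocyanin supplements can enrol and are told to keep their habits, so the cherry-arm change from baseline may be blunted and the primary contrast diluted

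*Protocol article*

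**What the plan says.** All references are to the Protocol article.

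- **Inclusion (section 2.2).** The only stability requirement concerns drugs: participants must "have maintained consistent use of medication for a minimum of 3 months". Diet and supplements are not mentioned.
- **Exclusion (section 2.3).** The list is one of medical conditions, opening with "Exclusion criteria for this trial include the presence of diabetes, HIV, rheumatoid arthritis, or any other autoimmune disease". Its only cherry-related item is that people with "known food allergies to cherries will also be excluded from participation".
- **Conduct during the trial (section 3.2.1).** The article states that "participants will be required to maintain their habitual patterns throughout the intervention period". They are also "asked to keep a 4-day diet diary prior to the baseline assessment and before the follow-up examination". The article then claims: "This will ensure that there are no differences in dietary patterns between groups". Medications and comorbidities are to be recorded; supplements are not named.
- **Placebo (section 3.1.2).** "A 30 mL dose of placebo concentrate includes 0 mg of anthocyanins". This describes the product, not the participant's total intake.
- **Analysis (section 3.4).** The treatment effect is the between-arm difference in change from baseline to 6 weeks. The arms are also compared on experimental anthocyanin intake; background intake is given no role.

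**The concern.** The introduction presents 6 weeks of bilberry as having improved endoscopic activity and faecal calprotectin in people with this disease, and suggests that cherry may do more. On that premise, someone already taking such a product may enter with part of the benefit in hand. Section 1.1 adds that the investigators' own research "has revealed a strong willingness to take Montmorency tart cherry supplementation in patients with UC", and section 2.5 recruits through a patient charity and social media. Some users among the volunteers are therefore plausible, although their number is unknown.

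The habitual-patterns rule keeps such a person on the product. If that person is in the cherry arm and gains less from the added dose, the arm's mean change shrinks. The same would apply to calprotectin, the cytokines and the microbiome measures. In a trial of 40 with no visible spare power, a null result would be harder to interpret. The diary does not close the gap: it covers 4 days before each of two visits, and no action is attached to what it shows.

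**Working it through.** **1. What the rules do, taken together**

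| Person | Can enrol? | Instruction | Expected effect on the change from baseline |
|---|---|---|---|
| Non-user, either arm | Yes | Keep habits | As planned |
| Steady user, placebo arm | Yes | Keep using | Little or none: same background at both visits |
| Steady user, cherry arm | Yes | Keep using, plus trial product | Possibly blunted, if the added dose gives less benefit |
| Non-user who starts a product | n/a | Would break the instruction | Not a consequence of the rule as written |

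Only the third row is a route to dilution that follows from the text.

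**2. The plan's own sample size (section 2.4)**

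Inputs: 20 per arm, 20% attrition, α = 5%, a difference of 6.5 points, and "β = 0.80" read as 80% power. No SD and no sidedness are given, so the figure of 20 cannot be reproduced independently. A two-sided test is assumed and the SD is back-solved.

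- Completers per arm: 20 × (1 − 0.20) = 16.
- Normal approximation: SD = 6.5 / [(1.960 + 0.842) × √(2/16)] = 6.5 / 0.991 = 6.56.
- A t-test version gives d = 1.024 and SD = 6.35.

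**3. Dilution**

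Let f be the share who contribute no contrast. The expected difference is 6.5 × (1 − f). Power is approximately Φ[2.802 × (1 − f) − 1.960]. Once 80% power is taken as the start, this depends only on f and not on the SD. Completers needed to restore 80% are 16 / (1 − f)², then divided by 0.80 for attrition, rounding up each time.

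| f | Difference | Power | Completers per arm | Enrolled per arm |
|---|---|---|---|---|
| 0 | 6.50 | 80% | 16 | 20 |
| 5% | 6.18 | 76% | 18 | 23 |
| 10% | 5.85 | 71% | 20 | 25 |
| 20% | 5.20 | 61% | 25 | 32 |
| 30% | 4.55 | 50% | 33 | 42 |

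The t-test powers agree to within about 0.1 percentage point.

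The table assumes that a user loses the whole effect. If users lose only a fraction k, replace f by f × k. For example, 20% users each losing half gives 0.20 × 0.5 = 10%, hence 71% rather than 61%.

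**4. Chance imbalance**

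Suppose 4 of the 40 are users (10%) and the arms are 20 and 20. The chance that 3 or 4 of them fall in the cherry arm is [C(20,3) × 20 + C(20,4)] / C(40,4) = (22,800 + 4,845) / 91,390 = 0.30. With 3 of 20, the share in that arm is 15% rather than 10%. This is chance variation rather than bias, but in arms this small it is not negligible.

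**The case against.** **The article is condensed.** Screening questions and participant instructions may sit in a full protocol that is not shown. This stands as a reason to check that document first. It does not dispose of the point, which rests on what the article prints: eligibility lists with a cherry-specific item, an affirmative instruction to keep habits, and a claim that the diaries guarantee dietary equality.

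**A legitimate add-on design.** Testing a supplement on top of habitual diet is a reasonable choice, and the article says it follows earlier cherry trials. That holds for ordinary food. It is weaker for concentrated products of the same class as the intervention.

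**No ceiling is shown.** Everyone enrolled must have a Mayo score of 3 to 10, so an existing user still has room to improve. This also stands, and is why blunting is only a possibility.

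A reader might infer stronger versions, which the documents do not support:

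- *That the baseline already carries the treatment effect.* This could be true only of users who enrol. No user rate is given, and section 1.1 reports willingness, not current use.
- *That background use in the placebo arm destroys the comparison.* The contrast is in change from baseline. With habits steady, the arms still differ by the randomised product.
- *That placebo participants are free to start a retail product.* Starting one would already breach the habitual-patterns rule.
- *That the stated objective is to show absence of effect.* Section 1.2 says the aim is to assess the impact against placebo.

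**Conclusion.** The point holds in a limited form. As printed, the criteria admit current users of tart cherry or other anthocyanin supplements, and the conduct rule keeps them on those products. Any resulting bias runs towards no difference and arises through a blunted response in cherry-arm users; uneven numbers of users between small arms can add to it by chance. Separately, the statement that the diaries ensure dietary similarity is wrong as worded: they can only record it.

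The illustrative size is a fall in power from 80% to about 76%, 71% or 61% for 5%, 10% or 20% contributing no contrast. This rests on an assumed user rate, an assumed two-sided test, a planned power of exactly 80% with 16 completers per arm, and complete loss of effect in users. With no users, or with users who respond fully, the loss is zero. The gap is worth closing because closing it is cheap, not because harm has been shown.

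**What to change.** 1. **Section 2.3:** exclude current users of tart cherry or other anthocyanin concentrate, juice or capsule supplements, unless they have stopped for a defined period before baseline. The sponsor should set that period.
2. **Section 3.2.1, conduct:** clarify that habitual diet continues, but that no non-trial cherry or anthocyanin supplement is taken between baseline and week 6. This belongs with item 1: a restriction alone would make existing users stop at baseline and could itself cause a change in the placebo arm.
3. **Section 3.2.1, recording:** record supplement use at both visits, alongside the diet diary and medication record already planned.
4. **Section 3.2.1, wording:** say that the diaries assess dietary similarity and change, not that they ensure it.

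The cost is about two protocol sentences, one screening question and one extra item at each visit. A few volunteers would be excluded or delayed. Ordinary food intake stays unrestricted. If the full protocol already contains such rules, the article only needs to state them and correct the diary wording.
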